## 5. TREATMENT of Subjects

### 5.1 Investigational product / treatment

INTERVENTION GROUP: culturally sensitive hypertension education

#### *Method*

The patients participating in the intervention group will get three consultations with a practice nurse (POH) of 20-30 minutes with an interval of three months. The method evaluated in this study, culturally sensitive hypertension education (CAHE), is an addition to the standard education method (the 5 A's \*) which is used to assist patients in dealing with high blood pressure and which is recommended by CVD guidelines of NHG (1).

*(5 A's: 1. Ask: question regularly and systematically about the current behavior; 2. Assess: determine the willingness to bring about behavioral change; 3. Advise: strongly recommend to achieve behavioral change; 4. Assist: assisting where possible through referrals, supportive treatment or medical intervention; 5. Arrange: investigate potential conditions for relapse prevention and make follow-up arrangements.)*

CAHE focuses on discussing culture-specific aspects of the patients' perspective on BP and treatment. The preliminary study showed that three sessions (consultations) often enough to essential aspects of the patients' perspective on hypertension with the patient. After the baseline assessment the POH will make appointments for the three sessions with the participant. A week before a scheduled session, the participant will receive a written reminders from the POH. The POH will record the sessions with an audio recorder, only after permission from the patient. The recordings will be used for the process evaluation.

#### *Contents CAHE*

The first session is mainly aimed at eliciting ideas, concerns and expectations on BP and treatment, using reflective listening, giving medical information about BP, matching both perspectives, and setting a target for the follow-up session. The two follow-up sessions focus on discussing patients' experienced barriers and increasing their motivation and skills for continuing to achieve their medication and life-style targets. The approach use in these session is derived from theories the medical anthropologist Kleinman (especially the distinction between professional and lay 'Explanatory Models'), (27) and recent approaches for improving adherence in hypertensive patients. (28)

*Treatment goals for the hypertension patient according to NHG clinical guideline):*

- *Blood pressure: reaching the following target blood pressures: SBP <140 mmHg and DBP <90 mmHg with appropriate use of medication. If necessary adjustment medication in consultation with GPs to reach the targets. If target with three agents are not achieved, SBP decrease of at least 10 mmHg acceptable.*
- *Lifestyle Changes (if necessary): Quit smoking, a maximum of 2 alcoholic drinks per day (women) or 3 (males); regular physical exercise: min 5 days a week 30 minutes biking / brisk walking / gardening etc.; Proper diet: low fat, min 1 time per week fatty fish, 200 grams of vegetables and 2 pieces of fruit daily, little salt; Optimal weight: BMI <25 kg/m^2, waist circumference 80 cm (women) / 94 cm (men). In order to achieve the lifestyle adjustments it may be necessary as an intermediate to refer the patient to a health care professional specialized in the field.*

The recommended method for providing CAHE consists the method described in the NHG guideline CVRM, supplemented with specific questions from the CAHE protocol that was developed in the previous study ("Under Pressure 1") . (26) In addition to this information leaflets can be yused which are tailored to the needs of Ghanaian and Surinamese

hypertensive patients and a map of neighbourhood facilities that support lifestyle changes for Ghanaian and Surinamese.

The session with Afro-Surinamese patients will be held in Dutch and with Ghanaian patients in English or if they prefer this in Dutch or in a combination of Dutch and English.

After three educational sessions the patients in the intervention group will be given the regular hypertension care.

Box 1 contains a summary of the sessions.

Box 1: Overview phases culturally sensitive hypertension education

| Sessions/topics                                                                       | Eliciting patient-perspectief                                      | Information from medical perspective                               | Tuning the two perspectives                                              | Increasing motivation to change behaviors |
|---------------------------------------------------------------------------------------|--------------------------------------------------------------------------------|--------------------------------------------------------------------------------|--------------------------------------------------------------------------|-------------------------------------------|
| Session 1:
What is hypertension?

Communication patient health care provider | Hypertension

Communication-barriers                                     | Hypertension                                                                   | Understanding of hypertension                                            |                                           |
| Session 2 and 3:
Managing hypertension

Education/treatment                  | -BP control
- Targets 
BP;
Lifestyle changes  | -BP control
- Targets 
BP;
Lifestyle changes  | Relate to patient-perspective 
+
Joint decision making | Motivational strategies       |

The health care professional providing CAHE:

In two intervention centers a POH will be responsible for providing CAHE. This POH will be appointed specifically for the purposes of this study and will receive a clear protocol and training and will be instructed not to provide information about CAHE to colleagues.

CAHE sessions with patients in the intervention group should preferably be held at the health care centers where the patient is being treated. The POH who is to be recruited for this study, must be trained in the principles of patient counselling according to the 5 A scheme. The specific training the POH will receive for the purpose of this consists of information about BP in patients of African origin, a training in how to work with the CAHE protocol in patients from the target groups. Use is made of the training manual that has been developed in the previous project (under-pressure-I).

After the T0 assessments, patients in the intervention group will receive three appointments for CAHE sessions with the POH (2 weeks, 3 ½ and 6 ½ months after T0 measurement) At these intervals the POH will also measure patients' BPs with an electronic device (Omron 705-IT) according to a standardized method, the treating POH. This is a standard component of hypertension education, both in the experimental intervention protocol and in the NHG protocol. At these points, we will also measure the self-reported adherence to medications and lifestyle advice through a short questionnaire. The POH will ask the patient to complete these lists in the waiting room.

#### CONTROL GROUP

The POH's in control centers give patients the usual care. The patients in the control group will be given an appointment at 3 ½ and 6 ½ months after the T0 measurement to get their repeat prescriptions for anti-hypertensive medications. A blood pressure reading will be performed by the treating POH with an electronic device (Omron 705-IT) according to a

standardized method. In all patients in the control group after 3 ½ and 6 ½ months self-reported adherence to medication and lifestyle advice will be measures via a short questionnaire. The POH will ask the patient to complete these lists in the waiting room

## **6. METHODS**

### **6.1 Study parameters / endpoints**

#### **6.1.1. Main study parameter / endpoint**

Difference between baseline systolic blood pressure and systolic blood pressure at 8 months past baseline.

#### **6.1.2. Secondary study parameters / endpoints (if applicable)**

Difference between baseline and 8 months past baseline regarding the following measures:

- Adherence to medication
- Adherence to lifestyle advice
- Mediating factors that may affect the way in which patients manage hypertension:
  - o beliefs about hypertension and medication / lifestyle changes
  - o motivation to use / medication to carry out lifestyle changes
  - o self-efficacy to use / medication to implement lifestyle changes
- Satisfaction with care
- Baseline demographics of potential confounders, such as age, gender, ethnicity, environment and other socio-economic circumstances are included in the study.

#### **6.1.3 Other study parameters (if applicable)**

A process evaluation will be conducted to provide insight into factors that may be relevant to determine the effect of the intervention:

- is the study conducted as planned (fidelity)?
- participation in the study
- Information on refusals to participate
- reasons for discontinuation in participating in scheduled consultations in study arms
- information about obstacles that arise in CAHE sessions (via tape recordings)
- Explanatory models, perceived barriers and facilitators for following medication and lifestyle advice; (via some in-depth interviews with patients from intervention and control groups)

### **6.2 Randomisation, blinding and treatment allocation**

Randomization takes place at the level of the health care centers. There are four health centers (clusters) needed for this study, two for the intervention arm and two for the control arm. Through a computer designed randomization list recruited centers will be divided into control centers and intervention centers. Once the centers have given their consent to participate, the randomization will be performed by an employee of the AMC Data Management Services team KEBB department of the AMC who is not involved in the study and blinded to the identity of the practices

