### 3. STUDY DESIGN

The study is designed as a cluster-randomized controlled trial (RCT), which will compare patients who receive CAHE and with those who only receive usual care. We will collect data on the level of the patient, but randomize at the level of health care centres. The main reason for choosing a RCT with cluster randomization instead of a RCT with randomisation at patient level is that with the latter study design contamination can easily occur between the intervention and control groups.

On the basis of an analysis of numbers of patients, four health care centers (clusters) are required for this study, two for the intervention arm and two for the control arm. Important selection criteria for health care centers are that they should treat a sufficient number of patients from the target groups and that the hypertension care takes place according to the NHG standard CVRM.

The four health centers participating in the study will be randomly assigned to the intervention arm or the control arm (1 to 1 ratio).

The randomization will be performed by an employee of the Data Management Services team of the KEBB department of the AMC who is not involved in the study and blinded to the identity of the practices. In the health centers that are assigned to the intervention arm enrolled patients will get the CAHE. In the health centers that are assigned to the control arm enrolled patients will get the usual care which is provided in the health care centers. It is assumed that intercluster variance will be low. Based on the inclusion criteria and the fact that patients are treated with the same standard NHG in all four centers, we assume that differences in the mean blood pressure of hypertensive patients from the four centers will be low. Because the intra-cluster correlation coefficient is a ratio of the low between cluster variation and the within cluster variation, the intra-cluster correlation (ICC) is estimated to be <3%.

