The EMRs contain no information on ethnicity, but this is an essential variable of this study. Therefore, as a second step in the selection, based on the selection procedure in step 1, a list of names of names will be produced without further information about the patients. From this list people with Afro-Surinamese and Ghanaian names will be selected. This method was previously used in the project Heebroedoe and projects at the Department of Social Medicine of the AMC. Therefore, a list of common Afro-Surinamese and Ghanaian names, is already available. In the latter studies the selection of patients by name was made by a GP or practice nurse. In the present study, it is of great importance to avoid selection bias. Therefore an independent person, who does not know the patients, will be ask to select patients with Ghanaian and Afro-Surinamese names from the list name matching. Only in case of doubt a GP or the POH may be consulted about the ethnicity of the patient. Once the list is ready the attending physician will be asked, if the selected patients are suitable to participate in the study, based on their health. During selection procedure additional information (retrospective, if available) will be recorded from the EMRs of potentially eligible patients on additional risk factors for CVD (f minutes of exercise per week, diet, salt intake, smoking, alcohol consumption, height / weight, BMI, waist circumference, glucose and lipids (total cholesterol , HDL-cholesterol, TG, LDL), and other conditions such as myocardial infarction, congestive heart failure) TIA, stroke, renal failure, microalbuminuria), dementia depression, schizophrenia or liver disease). This additional information will only be used, however, after the patient has given informed consent to participate in the study. The selected eligible patients will receive an invitation letter to participate in the study in English (Ghanaians) or Dutch (Suriname) on behalf of their GP during their next appointment or by mail. In this letter patients will be informed about the study and invited to participate. The invitation letter contains a form with a free return envelope in which the patient can indicate if he / she wishes not to be contact about the study. The patients who have not responded within two weeks will be contacted by telephone by the investigator who will provide them with information about the study and asks them if they are willing to discuss potential participation in the study. All written information about the study is available in the Dutch language (see Annex) and English.

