
#### **Informed Consent**

The patients in the intervention group and the control group will receive, prior to the T0 measurement, an oral explanation of the invitation letter with the opportunity to ask questions about the purpose and the further course of the study and the measurements. The participant is then asked if s/he want to sign the. "Informed consent" form. This informed consent is used to ask for permission:

- Participation in the study at T0 (baseline measurement)
  - Participation in the follow-up contacts
  - Permission to collect data relating from the EMR related to the treatment of hypertension.
- The informed consent form is available in the Dutch language (see Annex) and English

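### Nothing requires patient listing and physician suitability decisions to be finished before the centres are randomised, so the independent name selection protects only one step against selection bias

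*Protocol*

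**What the plan says.** **Randomisation.** Four centres are split two and two (sections 3 and 6.2). On timing, 6.2 says "Once the centers have given their consent to participate, the randomization will be performed". The draw is made by an employee "who is not involved in the study and blinded to the identity of the practices".

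**Patient entry.** Section 9.2, Recruitment, starts from a list drawn from the electronic records using the entry criteria. It then states a concern and a safeguard: "In the present study, it is of great importance to avoid selection bias", and "Therefore an independent person, who does not know the patients, will be ask to select patients with Ghanaian and Afro-Surinamese names". A GP or the practice nurse may be consulted where ethnicity is in doubt. Next, "Once the list is ready the attending physician will be asked, if the selected patients are suitable to participate in the study"; the sentence goes on to tie that judgement to the patients' health. Section 4.3 is looser: the treating physician may exclude a patient as unsuitable, and comorbidity is given only as an example. Patients then get an invitation letter, and the investigator telephones those who have not replied within two weeks.

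**Consent.** Section 9.2, Informed Consent, says: "The patients in the intervention group and the control group will receive, prior to the T0 measurement, an oral explanation of the invitation letter". Signature follows.

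**Masking.** Section 6.2, Blinding, covers the research nurse and research assistant who do the T0 and final measurements, and those who clean the data. Section 10.1 adds data management and analysis.

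**The concern.** In a cluster trial, a sound draw of centres does not by itself give comparable patients. If patients are identified and judged after the allocation is known, those who do this can, knowingly or not, let different kinds of patient into the two arms. A physician in an intervention centre might put forward patients thought likely to cooperate with education sessions; a physician in a control centre has no such reason. The arms could then differ at entry in ways that bear on the change in systolic pressure.

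The protocol recognises the risk and acts on it for name selection. The question is whether the steps after that are protected too. Recruiting more patients does not shrink a bias of this kind.

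**Working it through.** No figure in the protocol depends on this point, so the check is a trace of the order of events and of who is masked.

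**1. Order.** Section 6.2 makes centre consent the condition for the draw. No section places the list, the suitability decision or patient consent before it. Section 9.2 describes patients by group before they sign, which fits allocation coming first, although it does not prove it.

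**2. Who acts at each entry step.**

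| Step | Who | Room for judgement | Stated to be unaware of the arm? |
|---|---|---|---|
| Record search (9.2) | not named | little, criteria are set | no |
| Name selection (9.2) | independent person who does not know the patients | little | no, but does not know the patients |
| Doubtful ethnicity (9.2) | GP or practice nurse | some | no |
| Suitability (9.2, 4.3) | attending physician | yes, on health grounds in 9.2, wider in 4.3 | no |
| Telephone contact (9.2) | investigator | yes | no |
| Oral explanation and consent (9.2) | not named | some | not stated |
| T0 measurement (6.2) | research nurse and assistant | not an entry decision | yes |

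The independence safeguard covers the second row. The masking statement covers the last. The rows between them, where judgement is greatest, have neither.

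**3. Could the arm stay hidden during recruitment anyway?** T0 falls within two weeks of inclusion (6.3) and the first education session two weeks after T0 (5.1, 6.3). So sessions begin at most about 2 + 2 = 4 weeks after a centre's first inclusion. The 240 recruits in 4.4 over four centres average 240 / 4 = 60 per centre. Invitations go by mail or at the patient's next appointment (9.2), which suggests entry spread over time. Assuming sessions start on schedule for each patient and are held at the patient's own centre, as 5.1 prefers, an intervention centre that takes longer than about four weeks to enrol will show its arm while entry is still open.

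**4. Could it be detected or corrected later?** Section 8.3 corrects for baseline differences between arms, and the T0 interview (6.3) measures motivation, adherence, beliefs and self-efficacy. That helps for what is measured. Section 9.2 allows the risk-factor data extracted at selection to be used only after consent, so patients screened out or refusing cannot be compared with those enrolled on those data.

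**The case against.** The strongest reply is that the protocol nowhere says that anyone who decides on entry knows the arm.

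- **Order.** Centre consent sets the earliest time for the draw, not its place relative to the patient list. The reference to both groups in the consent section may just mean all patients; 6.3 uses similar wording for the pre- and post-tests. This stands: early allocation is the natural reading, not a stated fact.
- **Knowledge of the arm.** The education nurse is appointed for the study and told not to inform colleagues (5.1, 6.2). This limits the spread of content. It does not hide that such a nurse is seeing patients in that centre, and it is not a masking rule for physicians or the investigator.
- **Suitability.** The recruitment step in 9.2 is limited to health. That narrows the discretion there, but 4.3 leaves it wider and health itself is a matter of judgement.
- **Consent rates.** A reader might infer that patients offered extra sessions would agree at a different rate. The text does not support this. Section 9.2 describes one invitation letter differing only by language, session appointments are made after T0, and the person taking consent is not named.
- **Adjustment.** A reader might infer that adjustment is useless. That goes too far, since motivation and adherence are measured at T0. It cannot be relied on for what is unmeasured.
- **Dropout.** The 50% in 4.4 might be read as a sign of unwillingness to enter. It applies after recruitment (120 / (1 - 0.5) = 240) and says nothing about entry.

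**Conclusion.** The point holds as a gap in the order and masking of patient entry. The protocol randomises on centre consent and does not require the list, the name selection or the suitability decisions to be finished first, or those who make the later decisions to be unaware of the arm. Measured against the protocol's own aim, the safeguard is incomplete.

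It would be too strong to say that people who know the arm decide who enters, or that the safeguard is cancelled. Knowledge of the arm is inferred from the protocol's silence and from the visit schedule, and both the criteria-based list and the independent name selection remain in place.

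No size or direction can be given. The documents report no expected share of patients judged unsuitable or refusing, and no link between suitability and response, so any figure in mmHg would be invented. The sample size in 4.4 is not affected. The case for change is that the risk is avoidable at small cost.

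**What to change.** In sections 6.2 and 9.2, set this order:

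1. At all four centres, complete the record list, the name selection including doubtful cases, and the physician suitability decisions, and freeze the list. Only then run the randomisation or disclose its result.
2. Use the same telephone script in all centres, with a caller unaware of the centre's arm where existing staff allow. State who takes consent and whether that person is masked.
3. Report by arm the numbers listed, judged unsuitable, refused and enrolled. Section 6.1.3 already collects participation and refusals; the additions are the other counts and the split by arm.

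This does not ask for consent and T0 from every patient before disclosure. That would hold early patients back until their centre had finished enrolling, which conflicts with a first session two weeks after T0.

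The cost is that allocation, and so the start at the centres, comes somewhat later. Freezing the list needs no extra staff or procedure.

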#### **Blinding**

In order to ensure blinding the measurements will be carried out as follows:

1. For the purpose of the beginning (T0) and the final measurement a research nurse will blood pressure measurements and physical examinations in all participating health care centers and collect the batch of morning urine from the patients. For blood pressure measurements validated electronic devices will be used (Omron 705-IT). A research assistant will carry out the study's questionnaire to assess other outcome measures. The research nurse and research assistant will be blinded to the study arms to which centers are allocated..
2. In the two intervention centers a POH will be responsible for delivering CAHE. The POH will receive a clear protocol and training (see 5.1). S/he will also be instructed to provide no

information about the study or the patient education to colleagues. The POH's in control centers will give patients the usual care. The blood pressure measurement is a standard component of hypertension education, both in the intervention and usual care. The interim blood pressure measurements at 3, 6 and 9 months, will be carried out by the attending POH's with the above-described electronic devices. The use of a standardized measurement methods restricts the possibility of ascertainment bias.

3. There will be blinding during while entering and analyzing the data. All data from the intervention and control groups are stored in one data set and the researchers who are cleaning the data will be blinded to the study arms.

